### Eligibility criteria

#### Diagnostic criteria

MetS diagnostic criteria are based on the 2024 Chinese Guidelines for the Prevention and Treatment of Type 2 Diabetes Mellitus (16). Diagnosis requires the presence of three or more of the following criteria:
Abdominal obesity: waist circumference ≥90 cm for men, ≥85 cm for women.Hyperglycemia: fasting plasma glucose ≥6.1 mmol/L or 2-hour postprandial plasma glucose ≥7.8 mmol/L and/or previously diagnosed diabetes under treatment.Hypertension: blood pressure ≥130/85 mmHg and/or previously confirmed hypertension under treatment.Fasting triglycerides (TG) ≥ 1.70 mmol/L.Fasting high-density lipoprotein cholesterol (HDL-C) < 1.04 mmol/L.

#### Pattern diagnosis (syndrome differentiation) criteria for Qi deficiency and blood stasis

Diagnosis requires either (33):

At least one item from each of the main symptom categories ① and ②. Or at least two items from each of the secondary symptom categories ①, ②, and ③.

Main symptoms:
① Qi deficiency: shortness of breath, fatigue, lassitude, weak pulse.② Blood stasis: stabbing pain, fixed pain, pain aggravated by pressure, tortuous vessels, subcutaneous ecchymosis, dark purple tongue or with ecchymosis/petechiae, engorged sublingual veins, choppy pulse, absent pulse, or deep-stringy, stringy-slow pulse.Secondary symptoms:
① Qi deficiency: spontaneous sweating, reluctance to speak, pale tongue.② Blood stasis: squamous and dry skin, limb numbness or hemiplegia.③ Blood stasis: poor memory.To ensure diagnostic consistency across the six multicenter sites and to minimize selection bias, the following procedure has been established. At each study site, three physicians with the academic rank of associate chief physician or higher will be responsible for TCM pattern diagnosis. Prior to the initiation of patient enrollment, these three physicians will independently evaluate 10 standardized case videos. Their diagnostic agreements will be assessed using Cohen's Kappa coefficient.

According to established benchmarks (34), a Kappa value of ≥0.75 is required to confirm “substantial to excellent” inter-rater reliability. Only after achieving this threshold will the center be permitted to start recruitment. If the initial Kappa value is <0.75, the physicians will undergo refresher training and repeat the assessment until the required consistency is met.

### Inclusion criteria

Age ≥65 years.Meets the diagnostic criteria for MetS.Meets the pattern diagnosis criteria for Qi deficiency and blood stasis.High cardiovascular and cerebrovascular risk population, meeting any one of the following criteria (35):
4.1.History of myocardial infarction.4.2.History of stroke or transient ischemic attack.4.3.History of coronary, carotid, or peripheral arterial revascularization.4.4.Coronary, carotid, or lower extremity arterial stenosis >50%.4.5.Positive exercise stress test or documented symptomatic coronary artery disease by any cardiac imaging, or unstable angina with ECG changes.4.6.Chronic heart failure (NYHA class II-III).4.7.Chronic kidney disease (eGFR <60 mL/min/1.73m^2^).

### Exclusion criteria

Secondary dyslipidemia, hypertension, or hyperglycemia.Type 1 diabetes mellitus.History of allergy to the study drugs.Acute coronary or cerebrovascular event within the past 14 days.Planned coronary, carotid, or peripheral arterial revascularization.Chronic heart failure (NYHA class IV).Undergoing continuous renal replacement therapy.End-stage liver disease.History of solid organ transplantation or on waiting list for solid organ transplantation.Malignancy.

### Withdrawal criteria

Does not meet the inclusion criteria (found after enrollment).Protocol violation regarding concomitant medication or failure to take study medication as prescribed, affecting outcome measures.Incomplete data affecting the judgment of efficacy and safety.Withdrawal from the trial for reasons other than adverse reactions or lack of efficacy.Loss to follow-up, etc.

### Intervention

This is an add-on study protocol. All participants will receive standard guideline-directed medical therapy. The interventions are as follows:

Treatment group: TJC, 0.3 g/capsule, orally, three capsules per dose, three times per day. Control group: TJC simulant (placebo), 0.3 g/capsule, orally, three capsules per dose, three times per day.

The placebo capsules, composed of starch, bitter acid, and dextrin, among other excipients, are identical to the investigational drug in appearance, size, color, dosage form, weight, taste, and odor. They are manufactured by Baoding Buchang Tianhao Pharmaceutical Co., Ltd.

The drug composition of TJC is: Pseudostellariae Radix (Taizishen), Salviae Miltiorrhizae Radix Et Rhizoma (Danshen), Coptidis Rhizoma (Huanglian), Astragali Radix (Huangqi), Gynostemmatis Herba (Jiaogulan), Dioscoreae Rhizoma (Shanyao), Atractylodis Rhizoma (Cangzhu), Scrophulariae Radix (Xuanshen), Hirudo (Shuizhi), Malvae Verticillatae Fructus (Dongkuiguo), Puerariae Lobatae Radix (Gegen), etc. It is manufactured by Baoding Buchang Tianhao Pharmaceutical Co., Ltd.

Regarding standard treatment for MetS components and cardiovascular/cerebrovascular diseases during the intervention period, standard guidelines related to aspirin, statins, ACEIs or ARBs, metformin, SGLT2 inhibitors, and GLP-1 receptor agonists will be followed. Substitution with TCMs having similar components and/or effects to TJC is not permitted. Investigators must accurately record concomitant medications, and doses should be kept stable throughout the trial whenever possible.

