Traditional Chinese medicine (TCM) compounds, by virtue of their “multi-component, multi-target, multi-pathway” intervention characteristics, offer novel insights for the comprehensive management of MetS. Meta-analyses have shown that TCM or the combination of TCM and Western medicine can effectively improve metabolic syndrome and reduce cardiovascular and cerebrovascular risk (19–21). Tongmai Jiangtang Capsule (TJC) is an innovative proprietary Chinese medicine developed independently, derived from the classical empirical formula “Method for Boosting Qi, Activating Blood, and Dredging Collaterals.” Its main components include Astragalus membranaceus (Huangqi), Salvia miltiorrhiza (Danshen), Ligusticum chuanxiong (Chuanxiong), Hirudo (Shuizhi), and Pheretima (Dilong), among others. Modern pharmacological studies have confirmed that its core active ingredients (e.g., astragaloside IV, tanshinone IIA, ligustrazine) can ameliorate metabolic disorders through multiple mechanisms (22–26): On one hand, astragaloside IV can activate the AMPK pathway—a key energy sensor that not only enhances insulin sensitivity and inhibits hepatic gluconeogenesis but also exerts anti-inflammatory effects by suppressing NF-*κ*B signaling—thereby ameliorating metabolic disorders; tanshinone IIA can downregulate the expression of inflammatory cytokines (TNF-α, IL-6) in adipose tissue, alleviating IR. On the other hand, ligustrazine and hirudin can inhibit platelet overactivation, reduce hypercoagulability, and simultaneously improve vascular endothelial function and delay the formation of atherosclerotic plaques by modulating the endothelin-1 (ET-1)/nitric oxide (NO) balance. Preliminary studies have indicated that TJC has beneficial effects on both macro- and micro-vascular complications of diabetes, with a good safety profile (27–32); however, its impact on hard cardiovascular and cerebrovascular endpoints (e.g., myocardial infarction, stroke, cardiovascular death) remains unclear.

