### Study procedure

The schedule of study procedures is outlined in Table 1. The study will include a screening/baseline period, a treatment period, and a follow-up period. The screening/baseline period will last 2 weeks, the treatment period will be 26 weeks, and the follow-up period will be 26 weeks. Patients will be required to provide written informed consent after a complete explanation of the study during the screening period.

**Table 1 T1:** Study schedule.

Research phase	Screening/baseline	Treatment phase			Observation phase after intervention
Number of visits	Visit 1	Visit 2	Visit 3	Visit 4	Visit 5
Visit time point	D-7–0	Week 4 ± 4 days	Week 12 ± 4 days	Week 26 ± 4 days	Week 52 ± 4 days

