### Sample size calculation

This is a two-arm, randomized, controlled superiority trial with a placebo control group and a TJC group. Using the composite primary outcome measure and a superiority test for proportions for sample size estimation. Based on literature, the estimated difference between the two groups is 15% (27, 38). With a one-sided *α*=0.025 and power (1-*β*) of 90%, using PASS 15 software for a 1:1 allocation ratio, and accounting for a potential 20% dropout rate (due to loss to follow-up, refusal, exclusion, etc.), a minimum of 265 subjects per group is required, resulting in a total sample size of at least 530 subjects.

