## Discussion

Driven by the high prevalence of MetS, its associated elevated cardiovascular and cerebrovascular risk, and the current lack of clarity regarding the effect of Tongmai Jiangtang Capsule—a glucose- and lipid-lowering agent—on cardiovascular events in MetS patients, there is an urgent need to fill the gap in high-level evidence for TCM compounds in this domain, prompting the initiation of this study. The adoption of a multi-center, double-blind RCT design represents the current “gold standard” for validating intervention efficacy. The multi-center design, by enrolling patients from diverse geographical regions (North, East, South, Southwest, Northwest China) and lifestyles (urban/rural), significantly enhances sample representativeness and reduces the “selection bias” inherent in single-center studies. Compared to other TCM studies, the multi-center nature of this trial better aligns with the characteristics of MetS, which involves “multi-system involvement and high population heterogeneity,” thereby strengthening the generalizability of the findings.

Notably, this study sets the primary endpoint as 3P-MACE (including non-fatal myocardial infarction, non-fatal stroke, and cardiovascular death). This “hard endpoint” directly reflects clinical outcomes and holds greater clinical significance compared to surrogate markers commonly used in traditional studies (39) [e.g., carotid intima-media thickness [IMT], flow-mediated dilation [FMD]]. The secondary endpoints encompass metabolic parameters and vascular-related indicators, addressing the developmental cascade of MetS: “metabolism-vascular injury-cardiovascular events.” This “stratified endpoint design” breaks through the limitation of traditional TCM research that often “emphasizes symptoms over hard outcomes,” better aligning with the core requirement of modern evidence-based medicine for demonstrating “clinical value.”

TJC has been marketed for years. Previous clinical trials and observational studies indicate that its adverse reactions are primarily mild gastrointestinal discomfort, with no reports of severe hepatic or renal impairment, ensuring good patient tolerability. Multiple clinical studies suggest that TJC can improve insulin resistance, effectively alleviate diabetic neuropathy and nephropathy, and improve prognosis in diabetic patients with cerebral infarction (32, 40).

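### TJC is a marketed product, but current or recent users are not excluded, no washout is stated, and the reach of the ban on similar products in weeks 26-52 is unclear

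*Protocol article*

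**What the plan says.** - **Availability.** The Discussion states "TJC has been marketed for years". The six sites listed under Setting and participants are Chinese-medicine hospitals, and the Inclusion criteria require a TCM pattern diagnosis.
- **Exclusions.** The only item in the Exclusion criteria that concerns the study drug is "History of allergy to the study drugs". Current or recent use of TJC or similar products is not mentioned, and no washout appears anywhere in the article.
- **Periods.** Under Study procedure: "The screening/baseline period will last 2 weeks, the treatment period will be 26 weeks, and the follow-up period will be 26 weeks". Table 1 gives the screening/baseline window as D-7 to 0. It schedules the composite outcome measures at all five visits, including week 52.
- **The ban.** The Intervention section states "Substitution with TCMs having similar components and/or effects to TJC is not permitted". The sentence before it begins "Regarding standard treatment for MetS components and cardiovascular/cerebrovascular diseases during the intervention period". The sentence after it asks for accurate recording of concomitant medications and for doses to be kept stable throughout the trial where possible.
- **Composition.** The Introduction names Huangqi, Danshen, "Ligusticum chuanxiong (Chuanxiong), Hirudo (Shuizhi), and Pheretima (Dilong), among others" as main components. The Intervention section names eleven ingredients and ends in etc.; Chuanxiong and Dilong are not among the eleven.
- **Existing safeguards.** Table 1 records co-medications at every visit and previous history at Visit 1. The Withdrawal criteria include "Protocol violation regarding concomitant medication or failure to take study medication as prescribed, affecting outcome measures".

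**The concern.** The Study objectives pose an add-on question: does TJC on top of standard Western treatment improve glycolipid metabolism and reduce events? That question needs participants who are not already on TJC when they enter.

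If a current user is randomised, the TJC arm continues an existing treatment and the placebo arm stops one. The baseline measurement is then an on-drug value in both arms. If the effect of the earlier TJC persists for a time, placebo patients carry part of it into the trial and early between-arm differences shrink.

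The second part concerns the other end of the trial. Treatment stops at week 26 but outcomes are collected to week 52. If the ban lapses at week 26, a placebo patient may start the marketed product and a TJC patient may carry on with it. The follow-up half would then be neither a defined off-drug period nor a defined comparison with placebo.

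**Working it through.** **1. Can a current user be randomised?** Taking the printed criteria in turn:

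- Inclusion criteria: age, MetS, TCM pattern and high vascular risk. None refers to prior treatment with TJC.
- Exclusion criteria: allergy only, as regards the study drug.
- Screening: one or two weeks depending on the place read, with no instruction to stop TJC-like products.
- Withdrawal criteria: the medication item deals with violations. Use before enrolment violates no stated rule.

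So a current user is eligible as the text stands.

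**2. What does the ban cover?** Weeks 0-26 are covered on any reading. Time before randomisation is not mentioned. For weeks 26-52 the text supports two readings: the ban sentence itself is open-ended, while the opening of its paragraph refers to the intervention period. No other section settles this.

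**3. Does prior use by itself shrink the between-arm difference?** No. Write E for the TJC effect, and suppose a prior user already has E at baseline.

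- Randomised to TJC: change from baseline is about 0.
- Randomised to placebo with no carry-over: change is about -E.
- Difference in change: 0 - (-E) = E, the same size as in a new user.
- Randomised to placebo with a share c of the effect persisting: change is -(1 - c)E, so the difference is (1 - c)E.

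Attenuation therefore comes from c, the carry-over. The documents give no duration of effect. With 26 weeks off TJC before Visit 4, c is most likely to matter at the early visits (weeks 4 and 12).

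**4. The plan's own sample size.** Inputs from the Sample size calculation: "the estimated difference between the two groups is 15" percentage points, one-sided alpha 0.025, power 90%, 1:1 allocation, 20% dropout, 265 per group. Evaluable per group: 265 x 0.8 = 212. The event rates are not stated, so the figure cannot be checked uniquely. An assumed 43% against 28% reproduces it with the pooled formula:

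n = [1.960 x sqrt(2 x 0.355 x 0.645) + 1.282 x sqrt(0.43 x 0.57 + 0.28 x 0.72)]^2 / 0.15^2 = 211.8, rounded up to 212; 212 / 0.8 = 265.

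**5. Worst-case illustration.** Let a share f of placebo patients receive the full TJC effect over the whole endpoint period. The difference becomes 15 x (1 - f) points. Power = Phi(difference / SE - 1.960), with unpooled SE and 212 per arm.

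| Assumed control rate | f | Difference | SE | Power |
|---|---|---|---|---|
| 43% | 0 | 15.0 | 0.0459 | 90% |
| 43% | 10% | 13.5 | 0.0458 | 84% |
| 43% | 20% | 12.0 | 0.0456 | 75% |
| 30% | 0 | 15.0 | 0.0399 | 96% |
| 30% | 10% | 13.5 | 0.0395 | 93% |
| 30% | 20% | 12.0 | 0.0391 | 87% |

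These are upper bounds for the stated f. Full exposure throughout would require use in weeks 0-26, which the ban already covers. If use is confined to weeks 26-52, and the contrast is assumed to build evenly over 52 weeks, an exposed patient loses at most 26/52 = half of it. Then 20% of placebo patients starting TJC after week 26 corresponds to the f = 10% row at most.

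**6. Composition.** Three of the five components named in the Introduction (Huangqi, Danshen, Shuizhi) recur among the eleven in the Intervention section; two do not. Both lists are open-ended, so this is not a strict contradiction.

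**The case against.** The case against is substantial, and much of it stands.

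- **The ban is not expressly limited.** A reader might infer that it is written for the intervention period only. The sentence carries no such limit, the phrase belongs to the sentence before it, and the sentence after it speaks of the whole trial, though about dose stability. Only an unclear scope can be claimed.
- **On-TJC baselines do not pull the contrast to zero.** Step 3 confirms this; only carry-over attenuates. Abrupt stopping in the placebo arm could even widen the difference.
- **The power figures are not estimates for this trial.** The exposure shares have no source in the documents, the 43% control rate was chosen because it returns 265, and full exposure is an extreme assumption.
- **A null result would still be readable.** Randomisation balances prior use on average, and even the worst cases above keep 75% to 93% power.
- **Use after week 26 can be part of the question.** Under intention to treat, it can be counted as treatment policy.
- **Use is recorded** at every visit, and violations are dealt with in the Withdrawal criteria.
- **The ban also covers similar effects**, so a product absent from one component list can still be caught.

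What remains is narrower. Recording use does not decide who may be randomised, and the Withdrawal criteria cannot reach use that breaks no rule. A treatment-policy reading of weeks 26-52 is legitimate, but whether use in that period is permitted should be clear from the text.

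**Conclusion.** The point holds as a gap in eligibility and an unclear scope of the ban. As printed, current or recent users of a marketed study drug can be randomised, and for them the trial answers a continue-or-stop question, not the add-on question in the Study objectives. Any carry-over would attenuate the contrast, mainly in the early metabolic and symptom measures and less plausibly in the primary endpoint. Whether similar products are barred in weeks 26-52 cannot be determined, although the composite outcome is still collected at week 52.

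The size is unknown. The documents give neither the share of prior or later users nor the duration of effect. The 84% and 75% figures rest on an assumed 43% control rate, the planned 15-point difference, 212 evaluable per arm, and full exposure of 10% or 20% of placebo patients. They mark a worst case.

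Two stronger readings are not supported: that prior use biases the trial in favour of one arm, and that a null result could not be interpreted. This is a cheap improvement to the design, not a flaw that invalidates it.

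**What to change.** 1. **Eligibility.** Add to the Exclusion criteria current or recent use of TJC or of products covered by the ban in the Intervention section, with the interval set by the sponsor. Record past use explicitly at Visit 1.
2. **Scope of the ban.** State the period it covers and reconcile that with the period over which the primary endpoint is counted. Use the existing co-medication row in Table 1 to identify TJC and similar products, so that a sensitivity analysis can take account of such use.
3. **Reconcile the text.** Align the composition given in the Introduction and the Intervention section, so that sites apply the ban from one list. Align the screening length (2 weeks in the Study procedure text, D-7 to 0 in Table 1).

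The cost is a short amendment, one eligibility line and one case-report-form item. The downside is a small loss of eligible patients at the sites. No change to the sample size follows from this point.

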### Study procedure

The schedule of study procedures is outlined in Table 1. The study will include a screening/baseline period, a treatment period, and a follow-up period. The screening/baseline period will last 2 weeks, the treatment period will be 26 weeks, and the follow-up period will be 26 weeks. Patients will be required to provide written informed consent after a complete explanation of the study during the screening period.

**Table 1 T1:** Study schedule.

Research phase	Screening/baseline	Treatment phase			Observation phase after intervention
Number of visits	Visit 1	Visit 2	Visit 3	Visit 4	Visit 5
Visit time point	D-7–0	Week 4 ± 4 days	Week 12 ± 4 days	Week 26 ± 4 days	Week 52 ± 4 days
**Data collection**					
Written informed consent	□				
Inclusion/exclusion criteria	□				
Demographics	□				
Obtain central random number	□				
Previous history, medical history, and allergies	□				
Comorbidities and co-medications	□	□	□	□	□
Safety evaluation					
Vital signs and physical examination	□	□	□	□	□
Blood routine, Urine routine, Fecal routine	□		□	□	
Liver function(ALT, AST, ALB), kidney function(UN, Cr, UA, eGFR)	□		□	□	
12-Lead ECG	□		□	□	□
Efficiency evaluation					
Composite outcome measures	□	□	□	□	□
Preset exploration indicators	□	□	□	□	□
BMI, waist to hip ratio, body fat analysis	□	□	□	□	□
Blood glucose, blood lipids, blood pressure	□		□	□	□
Fasting insulin, C-peptide, HOMA-IR	□		□	□	□
Cardiovascular and cerebrovascular risk index	□		□	□	□
Troponin, cardiac enzymes, BNP	□		□	□	□
Vitamin D	□			□	□
UACR	□		□	□	□
Cardiac color doppler ultrasound	□			□	□
Neck vascular ultrasound	□			□	□
Traditional chinese medicine syndrome points	□	□	□	□	□
Quality of life rating	□	□	□	□	□
Omics analysis	□			□	

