### Pre-specified exploratory outcomes

Composite cardiovascular outcome (cardiovascular death, non-fatal MI, non-fatal stroke, coronary revascularization, or hospitalization for unstable angina or heart failure).All-cause mortality.Renal and glucose-related retinal microvascular composite outcomes.
3.1.Renal composite outcome: New-onset persistent macroalbuminuria (UACR >300 mg/g), or persistent doubling of serum creatinine from upper limit of normal or eGFR <45 mL/min/1.73m^2^, or requiring continuous renal replacement therapy or death due to renal disease.3.2.Diabetic retinopathy microvascular composite outcome: Requiring retinal photocoagulation or intravitreal injections, vitreous hemorrhage, or blindness.

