### Safety assessment

1.Safety evaluation indicators

Safety evaluation indicators include physical examination, vital signs (heart rate, respiration, temperature, blood pressure), laboratory tests, and adverse events (AEs), including severe adverse events (SAEs). Laboratory tests include complete blood count, urinalysis, blood biochemistry, and 12-lead ECG. Blood biochemistry will specifically include alanine aminotransferase (ALT), aspartate aminotransferase (AST), albumin (ALB), creatinine (Cr), blood urea nitrogen (BUN), and estimated glomerular filtration rate (eGFR).

During the treatment period, investigators must carefully observe and record all AEs and unexpected toxic side effects (including symptoms, signs, and laboratory abnormalities). Regardless of whether an AE is considered related to the investigational product, it must be documented in detail in the case report form (CRF), including time of onset, symptoms, signs, severity, duration, laboratory values, treatment administered and outcome, time elapsed, and follow-up time.
2.Clinical Events Committee and Independent Data Monitoring CommitteeA Clinical Events Committee (CEC) comprising a cardiologist, a neurologist, and an imaging specialist has been established. The CEC will adjudicate all suspected cardiovascular and cerebrovascular endpoints (including 3P-MACE) and all serious adverse events (SAEs) in a blinded manner using pre-defined diagnostic criteria.

An Independent Data Monitoring Committee (IDMC) composed of a cardiovascular specialist, a neurologist, and a biostatistician has also been established. The IDMC is independent of the sponsor and investigators.
3.Pre-specified SAEs related to TJC componentsIn consideration of the Hirudo (Shuizhi) component, the following events are pre-specified as SAEs requiring immediate reporting and adjudication:① bleeding requiring platelet transfusion or hospitalization; intracranial hemorrhage; gastrointestinal bleeding requiring transfusion; clinically significant mucosal bleeding requiring medical intervention; ② prolongation of APTT or PT > 1.5× upper limit of normal (ULN); platelet count < 50 × 10⁹/L; ③ ALT or AST elevation > 3× ULN; eGFR reduction > 30% from baseline or < 45 mL/min/1.73 m^2^; serum creatinine doubling from baseline.

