4.Blinded interim safety reviewA pre-specified blinded interim safety review will be conducted when 265 participants (50% of the planned sample) have completed 12 weeks of treatment. The IDMC will review the incidence of SAEs that are possibly, probably, or definitely related to the investigational product, without being unblinded to treatment assignment. If the pooled incidence of drug-related SAEs exceeds a pre-defined safety threshold (based on historical data of TJC and similar herbal products), the IDMC may request unblinding of group assignments to assess whether the signal is disproportionate. The IDMC may then recommend early trial termination, protocol modification, or continuation. All recommendations will be documented and submitted to the ethics committee.
5.Emergency unblinding procedureIf a serious adverse event (particularly bleeding) requires knowledge of treatment allocation for clinical management, the investigator may request emergency unblinding through the trial coordinating center. Upon verification, the investigator will be informed of the patient's group assignment within 4 h. The reason, date, and outcome will be recorded in the CRF and reported to the IRB and IDMC within 24 h. All SAEs will be followed until resolution or stabilization.

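### Table 1 schedules no creatinine or eGFR after week 26, although the exploratory renal composite uses both and its UACR leg is scheduled to week 52

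*Protocol article*

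**What the plan says.** Under Pre-specified exploratory outcomes, item 3.1 builds the renal composite from two laboratory legs and two clinical ones. The albuminuria leg is "New-onset persistent macroalbuminuria (UACR >300 mg/g"). The creatinine/eGFR leg is "persistent doubling of serum creatinine from upper limit of normal or eGFR <45 mL/min/1.73m^2". The clinical legs are renal replacement therapy and renal death. The article states no confirmation interval for persistence.

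Under Study procedure, "the treatment period will be 26 weeks, and the follow-up period will be 26 weeks", and the last visit is Visit 5 at week 52.

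In Table 1, creatinine and eGFR appear by name in one row only, "Liver function(ALT, AST, ALB), kidney function(UN, Cr, UA, eGFR"), which is ticked at Visits 1, 3 and 4. UACR has its own row, ticked at Visits 1, 3, 4 and 5. A further row, "Preset exploration indicators", is ticked at all five visits, and the article does not say what it contains.

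Under Safety assessment, the events pre-specified as serious include "eGFR reduction > 30% from baseline or < 45 mL/min/1.73 m^2^; serum creatinine doubling from baseline". The emergency unblinding item in that section adds: "All SAEs will be followed until resolution or stabilization".

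**The concern.** The two laboratory legs of one composite are scheduled over different lengths of time. Albuminuria is tested through the off-treatment half of the trial, while creatinine and eGFR stop at the end of treatment. A site that follows Table 1 would draw blood at week 52 for glucose, lipids, insulin and troponin and would not run creatinine.

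Two things are at stake. A definition that asks for persistence needs a later value, and a creatinine doubling first seen at week 26 has no later scheduled value. And after week 26 the only scheduled laboratory test feeding the composite is UACR. Inclusion criterion 4.7 admits patients on the strength of eGFR below 60, so some participants may enter close to the threshold of 45 that the composite uses.

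**Working it through.** The plan gives no figure to reproduce here. The check sets the schedule beside the definition and counts weeks.

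**Inputs.** Visit weeks and ticks come from Table 1, and the definition from item 3.1.

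| Row | Baseline | Week 4 | Week 12 | Week 26 | Week 52 |
|---|---|---|---|---|---|
| Kidney function (Cr, eGFR) | yes | no | yes | yes | no |
| UACR | yes | no | yes | yes | yes |
| Exploratory indicators row | yes | yes | yes | yes | yes |

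**Step 1: scheduled detection.** One value suffices to detect, so the window ends at the last scheduled test.
- Creatinine/eGFR: week 26, 26/52 = 50%. The remaining 52 − 26 = 26 weeks have no scheduled test.
- UACR: week 52, 52/52 = 100%.

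**Step 2: scheduled confirmation.** Assume that persistence means two consecutive scheduled values. The window then ends at the last-but-one scheduled test.
- Creatinine (weeks 0, 12, 26): week 12, 12/52 = 23%. Onset in the other 52 − 12 = 40 weeks (77%) cannot be confirmed by a scheduled test.
- UACR (weeks 0, 12, 26, 52): week 26, 26/52 = 50%.

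**Step 3: the other reading of eGFR.** The sentence leaves open whether persistence applies to eGFR below 45 or only to creatinine doubling.
- If it applies, the eGFR component has the 12/52 window of step 2.
- If it does not, a single week-26 value qualifies and the window is 26/52 = 50%.

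Weeks 26 to 52 stay without a scheduled eGFR on either reading.

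**Step 4: does another row close the gap?** The exploratory indicators row is also ticked at week 4, when neither UACR nor kidney function is drawn. It therefore reads more naturally as recording of events than as a blood test, though the article does not settle this. If it is meant to include creatinine at week 52, it disagrees with the kidney-function row.

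**Step 5: with creatinine and eGFR added at week 52.** Detection rises from 26/52 to 52/52. Confirmation under the step 2 assumption rises from 12/52 to 26/52, equal to UACR. A change first seen at week 52 would still lack a later value, as it does for UACR now.

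**The case against.** A reader might infer that a change first seen at week 26 can never be confirmed and that a later one can never be found. The documents do not support that. An eGFR below 45, an eGFR fall of more than 30% and a creatinine doubling from baseline are all pre-specified serious events, adjudicated by the Clinical Events Committee and followed until they resolve or stabilize. That is a real route to confirming some week-26 findings, and it can also show whether they reverse. Adverse events are recorded at week 52 as well, so clinically recognised renal disease, renal replacement therapy and renal death can still be captured.

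What remains is narrower. The serious-event route is unscheduled and is not tied to the composite's persistence requirement. Its creatinine reference is baseline, whereas the composite uses the upper limit of normal, so the two definitions do not select the same participants. It also needs a test result to set it off, and none is scheduled after week 26: a silent change in that period triggers nothing.

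A reader might also infer that the composite under-counts renal events overall, or becomes essentially a UACR outcome. Neither is shown. The article gives no renal event rates. Criterion 4.7 sets no lower eGFR limit, and the exclusion criteria bar only continuous renal replacement therapy. The new-onset qualifier is attached to macroalbuminuria, so a participant who enters with eGFR below 45 could satisfy the eGFR component from the start, which pushes the count the other way.

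Finally, the length of the confirmation interval may properly be left to the full protocol or analysis plan, and its absence from an article is no fault. The blank week-52 cell is different: Table 1 is explicit visit by visit and fills the UACR cell in the same column.

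**Conclusion.** The mismatch between Table 1 and item 3.1 is real. Creatinine doubling first seen at week 26 has no scheduled confirmation, and creatinine or eGFR events arising in weeks 26 to 52 have no scheduled detection. Serious-event follow-up and adverse event recording fill part of the gap only.

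The firm figure is that 26 of 52 weeks have no scheduled creatinine or eGFR. The 12-of-52 against 26-of-52 comparison holds only if persistence means two consecutive scheduled values. For eGFR below 45 the window is 12 or 26 of 52 weeks, depending on whether persistence governs it. The net direction of any miscount is not established.

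Severity is minor. One leg of one exploratory composite is affected; the primary endpoint, the sample size and the significance level are not.

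**What to change.** Reconcile Table 1 with item 3.1 in one of two ways.

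- Tick creatinine and eGFR at Visit 5 (week 52), run on blood already drawn at that visit. The cost is one routine assay per participant and a one-cell change to the schedule, with no extra visit.
- Or state that the creatinine/eGFR leg of the composite covers only the 26-week treatment period. This costs one sentence and no test, but leaves the two laboratory legs with different follow-up, which should then be said openly.

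If the exploratory indicators row was meant to include a week-52 creatinine, say so and align the kidney-function row with it. The same edit can make clear whether persistence applies to eGFR below 45. Neither option requires fixing a particular confirmation interval here; that can stay with the full protocol or the analysis plan.
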